### Analysis Populations and Missing Data Handling (SPIRIT Item 20c)

#### Analysis Populations

Intention-to-treat (ITT) population includes all randomized participants, regardless of protocol adherence, withdrawal, or missing data. This population will be used for the primary analysis to maintain the advantages of randomization and reduce selection bias.

Per-protocol population includes participants who completed the full course of treatment, had no major protocol violations, and provided complete outcome data. This population will be used for secondary analysis to evaluate the efficacy under ideal conditions.

Safety population includes all participants who received at least 1 session of treatment. AEs will be analyzed based on this population.

#### Missing Data Handling

MI with 20 imputed datasets will be used to handle missing outcome data in the ITT analysis. The MI model will include the primary outcome, secondary outcomes, baseline characteristics, and variables associated with missingness (eg, treatment group, participating center, and adherence to treatment). For the per-protocol analysis, only complete cases will be included.

### Statistical Software and Significance Level

All statistical analyses will be performed using SPSS 26.0 (IBM Corp) or R 4.2.0 software (R Core Team). The 2-sided significance level will be set at α=.05, and no adjustment for multiple comparisons will be made for secondary outcomes to avoid type II errors, but the results will be interpreted with caution.

## Results

This study is a prospective RCT that has completed the study design and obtained ethical approval. This study was funded in June 2023. It was supported by the Project of Shanghai Key Discipline Construction Project of Traditional Chinese Medicine (Clinical Category): Digital Intelligence Acupuncture (shzyyzdxk-2024108); the Project of Shanghai Municipal Health Commission (20204Y0165, 20224Y0165); the National Natural Science Foundation of China (82205145); Shanghai “Rising Stars of Medical Talents”-Youth Development Program-Youth Medical Talents-Specialist Program (SHWSRS 2023‐062); the Youth Talent Lifting Project of the Chinese Society of Traditional Chinese Medicine (2023-QNRC2-A03); and the “Visit Famous Schools and Worship Famous Teachers” Project of Shanghai University of Traditional Chinese Medicine (079). The funders had no role in the design of the study, data collection, analysis, interpretation of data, or writing of the manuscript.

Participant recruitment is projected to start in mid-2026 and end in December 2027, with a planned recruitment of 196 participants from 5 clinical institutions. As of the submission of this manuscript, the research team has completed the training of researchers, the preparation of study materials (such as informed consent forms, CRFs, and scales), and the debugging of equipment (electroacupuncture devices and actigraphy devices). The baseline characteristics of participants will be collected after recruitment starts, including age, sex, tumor type, surgical method, time since surgery, PSQI score, ISI score, etc

Data collection will be completed in October 2027, including baseline assessment (wk 0), treatment process records (weekly), posttreatment assessment (wk 4), and follow-up assessment (wk 12). Actigraphy monitoring will be conducted at week 0, week 1, week 2, week 3, and week 4 to collect objective sleep data. AEs will be recorded in real-time during the study period.

Data analysis is expected to be completed in December 2027. The primary analysis will focus on the difference in PSQI score changes between the electroacupuncture group and the sham electroacupuncture group based on the ITT population. Secondary analyses will include comparisons of actigraphy indicators, ISI score, SOSGOQ 2.0 score, and PHQ-9 score between the 2 groups at posttreatment and follow-up. Subgroup and sensitivity analyses will be performed to verify the robustness of the results. Safety analysis will evaluate the incidence and severity of AEs in both groups. The study results are anticipated to be published in the first half of 2028.

The trial flow chart is illustrated in Figure 3.

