**Methods:**

This is a study protocol for a randomized controlled trial. We will randomly assign 196 patients with insomnia after spinal metastatic cancer surgery to the acupuncture group (n=98) or the control group (sham acupuncture group; n=98). All participants will be treated on the first day after surgery and receive 12 sessions in total (30 min per session, 3 sessions per wk for 4 weeks). The primary outcome is the change in Pittsburgh Sleep Quality Index score from baseline to post treatment (wk 4). The secondary outcomes include actigraphy records (sleep efficiency, number of sleep awakenings, total sleep time, sleep latency, and wake after sleep onset), Insomnia Severity Index, Spine Oncology Study Group Outcomes Questionnaire 2.0, and Patient Health Questionnaire-9. All results will adhere to the intention-to-treat principle and will be evaluated at baseline, posttreatment (wk 4), and follow-up (wk 12).

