Numerous randomized controlled trials (RCTs) have evaluated the efficacy and safety of electroacupuncture for cancer-related insomnia (CRI), but SM postoperative insomnia has unique characteristics that distinguish it from general CRI. First, the pathogenesis is more complex; SM surgery involves spinal structure reconstruction, which may cause persistent postoperative pain, limited spinal movement, and neurological irritation, all of which directly interfere with sleep initiation and maintenance. In contrast, general CRI is more often associated with systemic symptoms such as tumor-related fatigue, anxiety, and drug side effects. Second, the sleep disturbance pattern is specific; patients with postoperative SM often experience sleep fragmentation due to nocturnal pain and positional restrictions, while general CRI is more likely to present as difficulty falling asleep or early awakening. Third, the rehabilitation context differs; patients with SM are in a critical period of spinal function recovery, and sleep quality directly affects tissue repair and neurological function restoration, whereas general CRI has a more indirect impact on disease progression. These unique characteristics indicate that the efficacy and mechanism of electroacupuncture for SM postoperative insomnia may differ from those for general CRI, justifying the necessity of this targeted study.

Studies in recent years have further confirmed the multifaceted adverse impact of postoperative insomnia on patients with SM. In terms of physical recovery, insomnia can reduce the body’s immune function, inhibit the repair of damaged tissues, and delay the recovery of postoperative motor and neurological functions [11-13]. In terms of disease prognosis, insomnia can up-regulate the expression of cancer-promoting factors (such as IL-6 and TNF-α), increase the risk of tumor recurrence and metastasis, and reduce the overall survival rate of patients [14-16]. In terms of mental health, long-term insomnia is closely associated with anxiety, depression, and other negative emotions, which further aggravates the decline in quality of life [17,18]. A 2023 study by Kim et al [8] found that CRI can mediate the impact of sleep disturbance on disease progression fear in patients with postoperative lung cancer, highlighting the importance of intervening in insomnia.

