#### Inclusion Criteria

First, male or female participants who were aged 18 years or older. This age limit is set because adults have relatively stable physiological functions and can better cooperate with the treatment and evaluation process.

Second, patients diagnosed with SM based on cytological or histopathological features, and undergone SM surgery within 1‐2 weeks. This time interval is determined because sleep disturbance after SM surgery is most prominent within 1‐2 weeks postoperatively, and intervention during this period is more conducive to improving rehabilitation outcomes.

Third, the PSQI score was >11. Patients with chronic insomnia disorder (defined as insomnia lasting ≥3 months before surgery) are excluded. According to the validation study of the Chinese version of PSQI, a score >11 indicates moderate to severe insomnia, which is a reasonable threshold for selecting patients with clinically significant postoperative insomnia [31,32].

Fourth, have an estimated survival period of at least 6 months. This is to ensure that participants can complete the entire treatment and follow-up process, and avoid the impact of patient death on the study results. The survival period is estimated by the attending physician based on the patient’s tumor type, stage, treatment response, and other factors.

Fifth, consent to participation and completion of the full treatment process, and provide written consent.

Sixth, postoperative blood examination showed no obvious abnormality, indicating that the patient’s general condition is stable and can tolerate electroacupuncture treatment.

Finally, no history of shift work in the past 6 months. Shift work can independently affect sleep patterns and confound the study results, so such individuals are excluded.

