#### Analysis of Primary and Secondary Outcomes (SPIRIT Item 20a)

##### Primary Outcome Analysis

The primary outcome is the change in PSQI total score from baseline (wk 0) to posttreatment (wk 4). ANCOVA will be used to compare the between-group difference in PSQI score changes, with baseline PSQI score, age, gender, tumor type, and participating center as covariates. This method can adjust for potential confounding factors and improve the statistical efficiency of the analysis.

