### Future Directions

If the efficacy of electroacupuncture is confirmed in this study, future research can be carried out in the following directions: (1) optimize the treatment plan: explore the optimal acupoint combination, treatment frequency, and course of electroacupuncture for SM postoperative insomnia to further improve the therapeutic effect; (2) mechanism research: explore the mechanism of electroacupuncture in improving SM postoperative insomnia from the perspectives of neuroendocrinology, immunology, and circadian rhythm; (3) combined therapy: study the efficacy of electroacupuncture combined with other nonpharmacological therapies (such as cognitive behavioral therapy for insomnia and music therapy) in the treatment of SM postoperative insomnia; (4) expand the population: conduct studies in patients with SM with different tumor types, surgical methods, and disease stages to further verify the generalizability of the results; (5) long-term follow-up: extend the follow-up period to 6‐12 months to evaluate the long-term efficacy and safety of electroacupuncture; (6) individualized treatment: based on patient characteristics (such as age, gender, and tumor type), develop individualized electroacupuncture treatment plans to improve the precision of treatment.

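### The primary ANCOVA omits surgical method and time since surgery, both recorded at baseline; this forgoes a little precision but causes no bias

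*Protocol article*

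**What the plan says.** The Results section of the protocol article lists the baseline characteristics to be collected, among them "age, sex, tumor type, surgical method, time since surgery, PSQI score, ISI score". The Primary Outcome Analysis section compares the change in PSQI total score from week 0 to week 4 by ANCOVA, "with baseline PSQI score, age, gender, tumor type, and participating center as covariates". It gives two aims for the adjustment: dealing with potential confounders and gaining efficiency. The Secondary Outcome Analysis section uses the same covariates for the actigraphy measures and a similar ANCOVA for the other scales.

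Randomisation is in blocks stratified by center, with no other factor.

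On the role of the operation, the Introduction says that "SM surgery involves spinal structure reconstruction, which may cause persistent postoperative pain, limited spinal movement, and neurological irritation", and that these directly disturb sleep. The Inclusion Criteria require patients to have "undergone SM surgery within 1‐2 weeks", on the ground that "sleep disturbance after SM surgery is most prominent within" that window. Future Directions proposes to "conduct studies in patients with SM with different tumor types, surgical methods, and disease stages".

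**The concern.** Adjustment is meant to gain efficiency, so the covariate list should favour variables expected to predict the PSQI change. The article's own account of this insomnia centres on what the operation does to the patient. It gives no comparable sleep rationale for age or gender, yet those are adjusted for while surgical method is not. The Limitations section also names postoperative pain intensity as an unmeasured confounder; surgical method is plausibly related to it and is already to be recorded.

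With stratification by center only, a chance imbalance in surgical method is handled neither by design nor by analysis. At stake is some precision that needs no new data. The list is fixed in the article, so this is not a detail left to the SAP. Covariates also carry conviction only if they are named before the data are seen.

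**Working it through.** **The plan's own figure.** Inputs from Sample Size Calculation: difference 1.8, SD 3.9, two-sided alpha 0.05, power 90%, dropout 20%, 98 per group.
- n per group = 2 × (1.960 + 1.282)² × (3.9/1.8)² = 99.
- This is about the stated 98, but before dropout. Dividing by 0.8 gives 124 per group. That gap is a separate matter; here it only fixes the starting point.
- Completers: 98 × 0.8 = 78 per arm. Standard error = 3.9 × √(2/78) = 0.62. Noncentral t power (154 degrees of freedom, noncentrality 1.8/0.62) = 81.7%.

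**Bias and type I error.** In simulation (8,000 runs per setting, 78 per group), a pre-randomisation variable explaining 2–20% of the variance was left out. The mean estimate stayed at 1.79–1.81 against a true 1.8, and type I error was 4.9%. The only cost is precision.

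**Surgical method.** The documents give no effect size, so assume two groups split 50:50 that differ by d = 1 to 2 PSQI points.
- If the whole difference fell in the 4-week change, its variance share would be 0.25 × d²/3.9² = 1.6% (d = 1) to 6.6% (d = 2).
- If the difference is already present at week 0, baseline PSQI absorbs part of it. With equal SDs and a baseline-to-week-4 correlation r, the share of residual variance is about 0.5 × d² × (1 − r)²/[3.9² × (1 + r)]. At r = 0.3 this is 1.2% (d = 1) to 5.0% (d = 2). At r = 0.5 it is 0.5% to 2.2%.
- Simulation with the PSQI entry threshold applied gives about 1–4%.

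**Time since surgery.** If recovery is linear, the 28-day change is the same whatever the day of entry, so this variable explains none of the raw change. Only curvature matters.
- Assume exponential recovery of A points with time constant τ. The 4-week change for entry on day t is A × exp(−t/τ) × [1 − exp(−28/τ)].
- For A = 8, τ = 14 this is 4.20 on day 7 and 2.55 on day 14, a range of 1.65. The share is (1.65²/12)/3.9² = 1.5%.
- Over A = 4–8 and τ = 14–42 the share is 0.04% to 1.5%. With baseline PSQI in the model it is at most about 1%.

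**Both together:** about 1–5% of residual variance. Replacing 3.9 by 3.9 × √(1 − R²) at 78 per arm:

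| Extra R² | Power | Fall in standard error |
|---|---|---|
| 0 | 81.7% | – |
| 1% | 82.1% | 0.5% |
| 2% | 82.5% | 1.0% |
| 5% | 83.6% | 2.5% |

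A 5% gain equals about 156 × (1/0.95 − 1) = 8 completers, and a 1% gain about 2.

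**Chance imbalance in surgical method.** The upper 95% limit at 98 per arm is 1.96 × √(2 × 0.25/98) = 14 percentage points. Times 1 to 2 points, this moves that one trial's estimate by 0.14 to 0.28, or 0.22 to 0.45 standard errors, against a planned 1.8.

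**The case against.** The strongest reply is that nothing here is wrong. The list already holds the baseline value of the outcome and the only stratification factor. No section promises to adjust for every recorded variable, and a short prespecified list is legitimate. The sample size rests on an unadjusted t test, so no stated figure depends on these covariates. All of that stands and sets the ceiling on this point. An imbalance of the size shown is also already allowed for in the confidence interval.

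A reader might infer that recovery running from the day of surgery contaminates an endpoint timed from randomisation. The documents do not support this: recovery common to both arms cancels in the comparison, and linear recovery drops out of the raw change. Adjusting for baseline PSQI can bring back a little dependence on entry day, up to 3% of variance. That needs 0.4 points per day, an 11-point fall over 28 days (0.4 × 28 = 11.2) in both arms.

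A reader might also infer that the plan itself declares these variables prognostic. It does not. The Inclusion Criteria justify an entry window and claim no gradient inside it, the Introduction does not compare surgical methods, and Future Directions concerns generalisability. The case for surgical method is plausible, not documented.

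The spread in time since surgery is itself unclear. The abstract says "All participants will be treated on the first day after surgery", whereas the Inclusion Criteria place surgery 1–2 weeks before entry. Under the first statement the variable would hardly vary. These passages must be reconciled.

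Sparse cells are a fair worry, with several centers and tumor type already in the model and the number of surgical methods not given. Grouping the methods meets it.

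**Conclusion.** The point holds as a minor improvement resting mainly on surgical method. The omission does not bias the estimate or inflate the type I error. It gives up roughly 1–5% of residual variance, which takes power at 78 completers per arm from about 82% to about 82–84%, and leaves a chance imbalance in surgical method unadjusted.

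These figures rest on assumptions: a 1–2 point difference between two equally common groups of methods, entry on days 7–14, a baseline-to-week-4 correlation of 0.3–0.5, and SD 3.9 as the residual SD before the additions. If center or tumor type already captures part of the surgical-method effect, the gain is smaller. It would be larger if methods differ only in the later course.

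A reader might expect baseline ISI to add much because the PSQI entry threshold narrows the range of baseline PSQI. The documents give no correlation to support that. ISI overlaps with PSQI and is indirectly restricted by the same threshold.

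**What to change.** Before recruitment starts, add two covariates to the list in Primary Outcome Analysis:
- surgical method, grouped into a few categories defined in advance, with a rule for merging rare ones;
- days from surgery to randomisation, as a continuous term.

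Carry the same set into the secondary ANCOVAs that reuse the list. Baseline ISI may be added to the primary model but is optional. If the sponsor prefers the shorter list, one sentence giving the reason is enough.

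The cost is one line in the protocol and SAP and no new data. With k method categories the change uses (k − 1) + 1 = k degrees of freedom, a few out of 196 patients.

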**Figure 3. F3:**
[figure not shown]
The trial flow chart. ISI: Insomnia Severity Index; PHQ-9: Patient Health Questionnaire-9; PSQI: Pittsburgh Sleep Quality Index; SOSGOQ 2.0: Spine Oncology Study Group Outcomes Questionnaire 2.0.

## Discussion

### Principal Findings (Anticipated)

This study is designed to test the hypothesis that compared with the sham electroacupuncture group, the electroacupuncture group will show a significant reduction in PSQI score from baseline to posttreatment (wk 4), indicating improved sleep quality. Based on previous evidence, electroacupuncture is expected to perform better in objective sleep indicators (such as increased sleep efficiency, prolonged TST, reduced number of sleep awakenings, shortened SOL, and decreased WASO), have a lower ISI score (reduced severity of insomnia), an improved SOSGOQ 2.0 score (enhanced quality of life), and a lower PHQ-9 score (alleviated depressive symptoms). In addition, electroacupuncture is expected to have a low incidence of AEs, demonstrating good safety.

### Comparison With Previous Work

Existing studies have confirmed the efficacy of electroacupuncture in the treatment of general insomnia and CRI. For example, a multicenter RCT by Lee et al [28] found that electroacupuncture can improve the sleep quality of patients with CRI. However, these studies did not specifically target patients with postoperative SM, who have unique clinical characteristics such as postoperative pain, spinal instability, and neurological damage. Patients with SM often have more complex sleep disturbance mechanisms, and the efficacy of electroacupuncture may differ from that in other populations.

In addition, most previous studies used small sample sizes and single-center designs, resulting in limited generalizability of the results. This study adopts a multicenter design, recruits 196 participants, and uses strict randomization, allocation concealment, and blinding methods to reduce bias, which is expected to provide more reliable clinical evidence. The selection of acupoints in this study is based on Traditional Chinese Medicine theory and clinical practice, and the treatment parameters (frequency, current intensity, and needle retention time) are standardized in accordance with STRICTA guidelines, facilitating the replication of the study results.

### Appropriateness of Sham Acupuncture Methodology

There has been extensive debate in the acupuncture research field regarding whether sham needling should be performed at true acupoints or nonacupoints. Proponents of nonacupoint sham needling argue that it can better control for the nonspecific effects of needle insertion, while advocates of true acupoint sham needling emphasize that the anatomical and physiological characteristics of acupoints may affect the blinding effect. In this study, we chose to use the Streitberger placebo needle at the same acupoints as the treatment group, and this choice is justified for the following reasons:

First, it ensures the success of blinding. The Streitberger placebo needle has a blunt tip that cannot penetrate the skin, but it can move within the handle, creating the illusion of needle insertion. For patients with postoperative SM who may have limited knowledge of acupuncture, this design makes it difficult to distinguish between real and sham acupuncture. If nonacupoints were used, the different anatomical locations might lead to differences in skin sensation, increasing the risk of unblinding.

Second, it controls for acupoint-specific effects. By using the same acupoints in both groups, the only difference between the electroacupuncture group and the sham electroacupuncture group is the presence or absence of effective needling (penetration and electrical stimulation), which can accurately evaluate the specific therapeutic effect of electroacupuncture. Previous studies have shown that true acupoint sham needling with placebo needles is an effective control method in acupuncture RCTs, as it can minimize the impact of nonspecific effects, such as expectation and attention [46,47].

Third, it is consistent with the clinical scenario. The acupoints selected in this study are commonly used in the clinical treatment of insomnia. Using the same acupoints for sham treatment ensures that the treatment process is similar to clinical practice, improving the external validity of the study. A systematic review by Xie et al [36] confirmed the validity of the Streitberger placebo needle in Chinese populations, further supporting the appropriateness of our choice. Therefore, the chosen sham electroacupuncture design is methodologically appropriate and consistent with contemporary recommendations for acupuncture RCTs.

